#### Cognitive assessment

The validated Montreal Cognitive Assessment^56^ (MoCA): This test includes sections on visuospatial/executive function, naming, attention, language, abstraction and orientation to time and place. This test will be used as a screening test for cognitive function prior to inclusion in the trial. This will be collected at baseline (week 0) and follow-up (week 9).

The validated Cambridge Neuropsychological Test Automated Battery^57^(CANTAB) cognitive test battery will be used to assess specific cognitive function domains pre-post intervention. The test battery includes: (1) Motor screening task, (2) Paired Associated Learning, (3) Spatial Working Memory, (4) Reaction Time, (5) Rapid Visual Information Processing and (6) Delayed Matching to Sample. This assessment will take approximately 35 min to complete. Processing speed and executive functions from the CANTAB suite (http://www.cambridgecognition.com/academic/cantabsuite/battery) will be compiled to derive an executive function score. This will be collected at baseline (week 0) and follow-up (week 9)

#### Physical Activity and Social Participation Assessment

The Rapid Assessment of Physical Activity^58^ (RAPA) is a 9-item, self-administered questionnaire developed to provide an easily administered and interpreted means of assessing levels of physical activity among adults older than 50 years. RAPA evaluates a wide range of physical activity level, from sedentary to vigorous activity, as well as strength and flexibility training and takes 5 min to complete. It has adequate convergent validity and good criterion validity. This will be collected at baseline (week 0) and follow-up (week 8)

The WHO Disability Assessment Schedule V.2.0^59^ is an assessment which provides a global measure of disability. It covers the following domains of functioning: Cognition—understanding and communicating; Mobility—moving and getting around; Self-car—hygiene, dressing, eating and staying alone; Getting along—interacting with other people; Life activities—domestic responsibilities, leisure, work and school; Participation— joining in community activities. This will be collected at baseline (week 0) and follow-up (week 9)

#### Subjective questionnaires

The Activities-specific Balance Confidence Scale^60^ assesses patient’s perceived confidence for performing 16-activities of daily living without losing balance. Scores ≤67/100% indicate increased falls risk. This will be collected at baseline (week 0) and follow-up (week 9)

The Falls Efficacy Scale - Internation (FES-I) Short Form is a short, easy to administer tool measuring an individual’s level of concern regarding falling during social and physical activities inside and outside the home, whether or not the person actually does the activity. Level of concern is measured on a 4-point Likert scale (1=not at all to 4=very). It has excellent internal validity and test–retest reliability. Scores >10 for the short form have been suggested as cut points for indicating high concern about falling.^61^ This will be collected at baseline (week 0) and follow-up (week 9)

The EQ-5D^62^ is a standardised, valid and reliable simple, generic measure of health status for clinical and economic appraisal. The EQ-5D-5L has five dimensions (mobility, self-care, usual activities, pain/discomfort, anxiety/depression) and includes the EQ Visual Analogue Scale (EQ VAS). The respondent is asked to rate their health status on these five dimensions from 1 to 5, respectively, as no problems, slight problems, moderate problems, severe problems and extreme problems. The EQ VAS records the respondent’s self-rated health on a 20 cm vertical, VAS with endpoints labelled ‘the best health you can imagine’ and ‘the worst health you can imagine’. The respondent is asked to mark an X on the scale to indicate ‘how your health is TODAY’. This will be collected at baseline (week 0) and follow-up (week 9)

Environmental Analysis of Mobility^63^ scale is a self-report scale assessing the effect of the physical environment on community mobility. Twenty-four features of the physical environment are identified. For each feature, an encounter question (How often do you?) is paired with an avoidance question (How often do you avoid?). Subjects report on frequency of encounter and avoidance behaviour using a 5-point ordinal scale (never, rarely, sometimes, often, and always). The test–retest reliability of the questionnaire is good. This will be collected at baseline (week 0) and follow-up (week 9)

The Behavioural Regulation in Exercise Questionnaire^64 65^ is a 24-item questionnaire to assess motivation to exercise. Participants rate whether statements apply to themselves (or not) using a 5-point Likert scale ranging from 0 (not true for me) to 4 (very true for me). This will be collected at baseline (week 0) and follow-up (week 9)

#### User experience evaluation (HOLOBalance group only)

The System Usability Scale^66^ is a 10-item questionnaire that asks individuals to rate their experience of using the system on a 5-point Likert scale ranging from 1 (strongly disagree) to 5 (strongly agree). Example items include ‘I think that I wold like to use this product regularly’. This will be collected by the treating physiotherapist at week 6 only

The User Experience Questionnaire^67^ is a 26-item self-report questionnaire to assess a person’s experience of using a product. Participants rate the product between two contrasting attributes (eg, attractive vs unattractive) on a 7-point Likert scale. This will be collected by the treating physiotherapist at weeks 1, 3 and 6.

The NASA Task Load Index^68^ is a widely used, subjective, multidimensional assessment tool that rates perceived workload in order to assess a task, system or team’s effectiveness or other aspects of performance. The NASA TLX assesses work load on five 21-point VASs ranging from 0 (very low) to 21 (very high) for task demands including mental demand, physical demand and temporal demand. Questions from the NASA TLX will be integrated into the HOLOBalance tasks. These questions will be administered 20 times per participant in total

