### Blinding

This is a single (assessor) blinded proof-of-concept study. As this study is comparing a technology intervention (HOLOBalance) versus standard care it is not possible to blind the participants or the treating clinicians to the intervention provided. The blinded outcome assessor will collect all of the outcome measures at baseline and follow-up with a single assessor being used at each site. Each assessor will be required to attend a training session prior to data collection to ensure consistency across sites. The outcome assessor will be asked to record any incidences of unblinding and detail how this occurred. Due to the nature of this study, we do not foresee circumstances where emergency unblinding of the outcome assessor is required.

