### Interventions

Participants will be randomised to receive either the active intervention (HOLOBalance) or the control intervention (OTAGO HEP). Participants will be asked to perform their prescribed exercises daily, with each participant performing 40–60 min of rehabilitation per day (including rest breaks). Participants will receive home visits from their treating clinician at week 0, 3 and 6 to assess and progress their programme. All participants will have a telephone conversation with their treating clinician every week for the duration of their participation in the rehabilitation programme to discuss their exercise programme.

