### Active intervention: the HOLOBalance system

HOLOBalance is an augmented reality balance training programme based on evidence-based MSR protocols.^49 50^ MSR requires individuals to regularly perform exercises which challenge the balance system (eg, closed eyes, stand on foam), optimise vestibular balance function and have been shown to improve balance control in healthy older adults^49 50^ and people with vestibular balance dysfunction.^51–54^

Participants will be required to wear a series of body worn sensors (pressure detecting insoles, intertial measurement unit (IMU) and a heart rate monitor, figure 2) when performing the exercises so that (1) the computer software can assess the participants performance and (2) the user can interact with the system. HOLOBalance will provide prescribed exercises and exergames presented into the person’s home environment by ahead mounted augmented reality display and log the user’s interactions with the system (eg, number of sessions completed). HOLOBalance will display a holographic virtual physiotherapist (figure 3A) to provide instructions and demonstrate prescribed exercises. The HOLOBalance programme will include exercises to maximise opportunities for balance improvement and include turning the head while looking at a target, standing on foam, and walking while turning the head (eg, of gameplay, please see figure 3B, C, and for table of basic exercises please see table 1). In addition, participants will be given auditory and cognitive exercises in supplement to their balance training programme. For further information on the HOLOBalance intervention, please visit www.holobalance.eu.

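### The treating physiotherapist collects the SUS and UEQ from HOLOBalance participants with no stated safeguard, so these secondary single-arm ratings are at risk of favourable response bias

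*Protocol article*

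**What the plan says.** Under User experience evaluation (HOLOBalance group only), which is part of the secondary outcomes, the protocol article describes three instruments.

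- **SUS:** it "is a 10-item questionnaire that asks individuals to rate their experience of using the system". On collection: "This will be collected by the treating physiotherapist at week 6 only".
- **UEQ:** it "is a 26-item self-report questionnaire to assess" a person's experience of a product. On collection: "This will be collected by the treating physiotherapist at weeks 1, 3 and 6".
- **NASA Task Load Index:** "Questions from the NASA TLX will be integrated into the HOLOBalance tasks". No physiotherapist is named as collector.

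The Interventions section gives the clinician's role: "Participants will receive home visits from their treating clinician at week 0, 3 and 6 to assess and progress their programme". A weekly telephone conversation with the same clinician is added. The Blinding section states that "it is not possible to blind the participants or the treating clinicians to the intervention provided", and assigns the baseline and follow-up measures to a blinded assessor.

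**The concern.** The SUS and UEQ are opinions. They are given while treatment is under way, to the clinician who prescribes the programme and will be in contact again within the week. Some participants may soften criticism in that setting, so the likelier error is towards favourable answers.

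Three features make this worth correcting.

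- The ratings come from one arm. The reported result is the score itself, and there is no control score against which a shared leniency could cancel.
- Recruiting more participants narrows the confidence interval but does not reduce an error that runs in one direction.
- The article names the collector. This is a stated procedure, not an operational detail left to a fuller document.

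At stake is how far the usability and user-experience scores can be taken at face value when the study explores acceptability with quantitative as well as qualitative data, as its strengths and limitations list says it will.

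**Working it through.** The article gives no expected mean, standard deviation, threshold or anticipated bias for either scale, so there is no figure to reproduce. The check compares the sections.

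**1. Who collects what**

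| Measure | Arm | Collector or route | Section |
|---|---|---|---|
| Baseline and follow-up measures | Both | Blinded assessor | Blinding |
| HOLOBalance adherence | HOLOBalance | Logged by the system | Primary outcomes |
| NASA TLX | HOLOBalance | Built into the tasks | User experience evaluation |
| Exit interview | HOLOBalance | Interviewer not stated | Primary outcomes |
| SUS | HOLOBalance | Treating physiotherapist | User experience evaluation |
| UEQ | HOLOBalance | Treating physiotherapist | User experience evaluation |

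In the user-experience section, only the SUS and UEQ are assigned to the treating physiotherapist.

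**2. Is the collector independent of the programme?** No. Trial design and Interventions have the treating physiotherapist supervise the exercise, judge performance, prescribe, progress, visit and telephone. I take treating physiotherapist and treating clinician to be the same person; Table 2 lists the home visits under the physiotherapist, which agrees. The Blinding section confirms that this person knows the allocation.

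**3. Is there a safeguard?** The article describes no sealed, anonymous, online or third-party return for these two forms.

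**4. What would leniency do to the result?** Write the reported mean as the true mean plus b, where b is the average leniency. In a two-arm contrast with equal leniency, (m1 + b) − (m0 + b) = m1 − m0, so b cancels. With one arm the result is m1 + b, and b stays whole. Random error falls with the square root of n; b does not. The documents give no value for b.

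**5. Which conclusions are touched?** The Primary outcomes section names recruitment, compliance and drop-out for acceptability, plus exit interviews. Neither the SUS nor the UEQ is on that list, and HOLOBalance adherence is recorded automatically. No between-group comparison uses either scale. The article sets no usability threshold and no progression rule that depends on them.

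**6. When are the forms collected?** The SUS is at week 6 in both the text and Table 2. The UEQ is at weeks 1, 3 and 6 in the text, but at weeks 0, 3 and 6 in Table 2. Home visits are at weeks 0, 3 and 6. If the first UEQ falls in week 1, no home visit is scheduled then and the only planned contact is the weekly call. How a form would be collected at that point is unclear.

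**The case against.** The strongest case against is that this is a reasonable choice for a pilot. Its main points are these.

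- **Collecting is not asking.** The wording does not say that the physiotherapist reads out the items, watches completion or sees the answers. The UEQ is expressly self-report, and on the SUS the participant does the rating. This stands, and it is why the finding is a risk and not a demonstrated bias. It does not remove the point, because nothing stated keeps the answers from the physiotherapist.
- **The participant rates a product, not the clinician.** The article says "HOLOBalance will display a holographic virtual physiotherapist", which gives instructions and demonstrates the exercises. The human physiotherapist prescribes and supervises. This weakens the motive for courtesy but does not abolish it.
- **Other evidence exists.** A reader might infer that the SUS and UEQ are the only standardised ratings of the system. They are not: the NASA TLX is a further subjective rating, of workload, given 20 times per participant. A reader might also infer that lenient scores could by themselves carry an unusable system into a future trial. The article does not support that, since poor usability could also show in logged sessions, drop-out and exit interviews, and no decision rule rests on these scales.
- **Collection at a visit protects completeness.** The Introduction cites up to 50% loss to follow-up in such programmes. If dissatisfied users return fewer forms, remote return could replace response bias with non-response bias in the same direction. Chasing by the weekly call would also bring the same physiotherapist back in. This is fair and shapes the fix: the form should be completed and sealed during the visit where there is one.

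**Conclusion.** The point holds as a risk. An unblinded clinician who prescribes and supervises the programme collects two subjective, single-arm, secondary ratings of it, with no stated safeguard. A favourable shift is plausible and would enter the reported scores undiluted.

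Its size is unknown. Any figure in scale points would only restate whatever leniency per item one chose to assume, so none is given. A reader might infer that the scores are certainly biased upward; the documents establish neither that a shift occurs nor its direction. A reader might also infer that the acceptability conclusion as a whole is compromised; the named primary measures are not reached by this route, and no between-arm contrast is involved.

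The conclusion assumes that treating physiotherapist and treating clinician are one role, and that no safeguard in an unseen manual already covers the two forms. It is a modest point, worth acting on because the remedy is cheap. The disagreement over the first UEQ time point is a separate inconsistency.

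**What to change.** In User experience evaluation, replace collection by the treating physiotherapist, for both the SUS and the UEQ, with wording such as:

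*The participant completes the questionnaire in private at the scheduled contact and either seals it before handing it back or submits it online directly to the study team. The form states that the treating physiotherapist will not see the answers.*

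The physiotherapist then only hands over the form or link. Returns should go to a member of the study team other than the blinded assessor, because only HOLOBalance participants complete these forms and receiving one would reveal allocation.

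Reconcile the first UEQ time point between the text (week 1) and Table 2 (week 0), and state how the form is obtained if no home visit falls at that point.

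The cost is an envelope or online form, a line on the questionnaire and a short protocol edit, with no extra staff. The downside is possibly a few more missing forms. Completing and sealing the form during the visit limits this, and the number returned should be reported beside the scores, out of the number of HOLOBalance participants.

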Balance rehabilitation typically consists of personalised sets of exercises, defined by a healthcare professional and is the only effective treatment for balance disorders, irrespective of a person’s age.^32–34^ Although exercises are typically brief and easy to perform, there is up to 50% lost to follow-up rate in older adults in these programmes, and while supervision significantly increases compliance and effectiveness,^35^ it is costly to provide. To this end, many falls prevention programmes provide exercise programmes completed either in group settings or independently at home.^36–41^ These programmes have been shown to be effective in reducing falls rates in older adults, reducing falls by 30%–40% (dependant on target population), however, they are limited in that they either do not provide exercises to address vestibular function or dual task training,^37–39^ or these are not introduced until very late in the programme.^40 41^ This is despite promising evidence suggesting that combined cognitive and functional training may provide improvements beyond single task training.^42–44^ Similarly, rehabilitation programmes which address vestibular dysfunction (ie, multisensory rehabilitation, MSR programmes) have been developed for older adults at risk for falls and have shown substantial additional reduction of falls risk to standard programmes.^45–47^ These programmes require customised, expert-led interventions to optimise recovery, however, there is limited availability of experts to provide these individualised interventions and these may hinder their translation into clinical practice.

The HOLOBalance telerehabilitation platform has been developed to address this lack of expert physiotherapists. HOLOBalance will provide a customised and interactive falls rehabilitation programme that incorporates: (1) functional balance training, (2) multisensory exercises to improve balance function and (3) cognitive-motor training, for older adults at risk for falls. HOLOBalance will use off-the-shelf technologies to allow clinicians to provide an individualised balance rehabilitation programme for older adults who will be able to participate in at a time of their choice and in their home environment (for system description please visit www.holobalance.eu). This study protocol outlines the multisite randomised controlled proof-of-concept study to explore safety, feasibility and acceptability of the HOLOBalance telerehabilitation system.

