### Outcome measures

#### Primary outcomes

The primary outcomes will relate to the acceptability, safety and feasibility of providing the HOLOBalance intervention. Acceptability measures include; recruitment rate (percentage of eligible participants enrolled), compliance with interventions (percentage of prescribed sessions completed in HOLOBalance and control groups) and drop-out rates (number of drop-out in HOLOBalance and control groups). Exit interviews will be completed with participants that receive the HOLOBalance intervention to explore their experience of using the system, including perceived benefits, frustrations and recommendations. Interviews will be recorded, transcribed verbatim and subject to thematic analysis.

In the HOLOBalance group, adherence will automatically be monitored through the interaction with the system, and calculated as the number of prescribed balance exercises, auditory and cognitive training tasks completed per day, expressed as a percentage. In the control group, participants will be required to complete a daily exercise diary to report on their level of activity, whether they had completed their HEP session and whether they had performed their cognitive tasks. All participants will receive a weekly telephone call from the research physiotherapist to discuss any issues, their current progress and to remind them to complete their exercise diaries (if in the control group) which will be collected at their final outcome measure test session. The order of events for participants enrolled in this study is displayed in table 2.

**Table 2 T2:** Order of events for all participants enrolled in the HOLOBalance study

		Screening session	Baseline test session	Week 0	Daily	Weekly	Monthly	Week 3	Week 6	Follow-up test session	Week 9
Recruitment Procedures	Provide patient information sheet	X									
	Provide informed consent		X								
University-based data collection	Demographics		X								
	The MoCA		X							X	
	The RAPA		X							X	
	The WHODAS 2.0		X							X	
	The CANTAB		X							X	
	The ABC Scale		X							X	
	The FES-I		X							X	
	The EQ-5D		X							X	
	The EMA		X							X	
	The BREQ-3		X							X	
	Mini-BESTest		X							X	
	The FGA		X							X	
	Exit Interviews (HOLOBalance Group Only)										X
Usability Measures	The SUS								X		
	The UEQ			X				X	X		
Home-based interactions	Equipment installation and Removal (HOLOBalance Only)			X						X	
	Home visit from Physiotherapist			X				X	X		

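### As scheduled, the week 6 SUS and the week 9 exit interviews over-represent HOLOBalance participants who stayed

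*Protocol article*

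**What the plan says.** All places are in the protocol article.

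- **SUS.** User experience evaluation (HOLOBalance group only): "This will be collected by the treating physiotherapist at week 6 only". Table 2 agrees. This section falls under Secondary outcomes.
- **Exit interviews.** Primary outcomes: "Exit interviews will be completed with participants that receive the HOLOBalance intervention to explore their experience of using the system". The Table 2 row "Exit Interviews (HOLOBalance Group Only" carries one mark, in the week 9 column. Neither text nor table describes an interview or a SUS at withdrawal.
- **Other acceptability measures.** Primary outcomes names the recruitment rate, "compliance with interventions (percentage of prescribed sessions completed in HOLOBalance and control groups" and "drop-out rates (number of drop-out in HOLOBalance and control groups".
- **UEQ.** User experience evaluation: "This will be collected by the treating physiotherapist at weeks 1, 3 and 6". Table 2 marks weeks 0, 3 and 6 instead, and week 0 is also when the equipment is installed.
- **NASA TLX.** User experience evaluation: "Questions from the NASA TLX will be integrated into the HOLOBalance tasks", with 20 administrations per participant.
- **Background on loss.** The Introduction says of balance rehabilitation that "there is up to 50% lost to follow-up rate in older adults in these programmes". No drop-out rate is assumed for this trial.

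**The concern.** Acceptability is a primary outcome, and the exit interviews are part of it. Among the measures listed there, the interviews are the only one that asks participants about their frustrations with the system. People who stop early because the headset, sensors or games did not suit them are likely to know most about what needs fixing. The schedule places the SUS and the interviews after many of them would have gone. A usability score and a set of interview themes drawn mainly from those who stayed would look better than the experience of everyone allocated to HOLOBalance. They would also say little about causes of leaving that could be corrected before a larger trial, and those causes are hard to recover afterwards.

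**Working it through.** The article gives no figure to reproduce here: no expected drop-out, no SUS target and no acceptability threshold. The check is a reading of the schedule followed by an illustration.

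**Step 1: who contributes what, as scheduled**

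| Leaves HOLOBalance | UEQ | NASA TLX | SUS | Scheduled exit interview |
|---|---|---|---|---|
| Before week 3 | at most the first (week 0 or 1) | until use stops | no | no |
| Weeks 3 to 6 | first two | until use stops | no | no |
| Weeks 6 to 9 | all three | until use stops | yes | no |
| Stays | all three | yes | yes | yes |

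SUS loss is therefore driven by drop-out before week 6, and interview loss by drop-out before week 9. The NASA TLX measures workload, not reasons for stopping.

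**Step 2: the first UEQ**

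The text says week 1 and Table 2 says week 0. Home visits are at weeks 0, 3 and 6 (Trial design; Interventions; Table 2), so at week 1 the only scheduled contact with the physiotherapist is the weekly call. If Table 2 governs, the first UEQ coincides with installation, and the first one informed by continued home use is at week 3. Anyone who leaves before then gives no UEQ based on continued use.

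**Step 3: size of the effect on the SUS**

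Inputs:
- n = 60 in the HOLOBalance arm (Sample size).
- d = proportion leaving before week 6: assumed, 5% to 50%. The upper end borrows the Introduction's background figure.
- g = points by which leavers would score below stayers: assumed, 10 to 30, on a SUS scored 0 to 100. The article does not state the scoring.

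If stayers average m and leavers would average m − g, the full-arm mean is (1 − d)m + d(m − g) = m − dg. The respondents' mean m therefore overstates it by d × g. The number of respondents is 60 × (1 − d).

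| d | SUS respondents of 60 | g = 10 | g = 20 | g = 30 |
|---|---|---|---|---|
| 5% | 57 | 0.5 | 1.0 | 1.5 |
| 10% | 54 | 1.0 | 2.0 | 3.0 |
| 20% | 48 | 2.0 | 4.0 | 6.0 |
| 30% | 42 | 3.0 | 6.0 | 9.0 |
| 50% | 30 | 5.0 | 10.0 | 15.0 |

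**Step 4: the same point without assuming a gap**

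Suppose 80% of respondents find the system acceptable (an assumption). If no leaver would agree, the full-arm share is 0.80 × (1 − d). If every leaver would agree, it is 0.80 × (1 − d) + d. This gives 76% to 81% at d = 5%, 72% to 82% at 10%, 64% to 84% at 20%, 56% to 86% at 30% and 40% to 90% at 50%.

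**The case against.** The strongest objection is that acceptability is not measured by these two instruments alone. Drop-out and compliance are named primary acceptability measures in both groups, and the drop-out count includes every early leaver. The SUS is a secondary user-experience measure. A reader might infer that the plan lets only those who tolerated HOLOBalance judge its acceptability. The article does not support that, and computed on all randomised participants, drop-out and compliance are free of this selection.

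A reader might also infer that early leavers are barred from interview. The text offers interviews to those who receive the intervention, without limiting them to completers. The week 9 mark is a schedule entry, and a condensed article may leave withdrawal procedures to the full protocol. This stands: the point is about what is scheduled, not about an exclusion.

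Other sources reach people before week 6: the UEQ up to week 3, the in-task NASA TLX, the weekly calls, the system's usage log, and the recording of adverse events and implementation problems. So it would be too strong to say that reasons for leaving are hidden. What remains is that none of these is described as asking a leaver why they stopped, and the first UEQ may predate real use.

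It is tempting to add that collection by the treating physiotherapist inflates the scores. The article calls the UEQ a self-report form, and collecting a form is not the same as asking or scoring it. A different collection route is a preference and is not pressed here. Nor is assigning a low score to leavers who do not respond, since any such value would be arbitrary.

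Finally, the 50% figure is an upper background value for such programmes. It is neither a forecast for this trial nor a rate of loss by week 6.

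**Conclusion.** The point holds in a limited form. The SUS rule is explicit, so following it yields no usability score from anyone who leaves before week 6. As scheduled, the interviews have the same weakness up to week 9. Drop-out and compliance show how many left and how much was done, but not why, and the earlier questionnaires fill the gap only in part.

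The overstatement of mean SUS runs from 0.5 points (5% × 10) to 15 points (50% × 30), with 4 points at 20% and a 20-point gap. All of these rest on assumed drop-out and an assumed gap. If nobody leaves before week 6, or leavers would score the same as stayers, there is no overstatement. No stated figure is wrong, and the article gives no SUS threshold, so no documented decision is shown to change.

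The first UEQ time point is a separate, small but true contradiction between text and Table 2. Overall this is a worthwhile, inexpensive improvement and does not threaten the primary outcome.

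**What to change.** 1. **Collect at stopping.** Add a rule that any HOLOBalance participant who stops early is offered the SUS and a short exit interview by telephone at that time. Amend the SUS timing and the Table 2 interview row to match. If the full protocol already provides for this, say so.
2. **Report the denominator.** Give SUS respondents out of all randomised to HOLOBalance, show SUS results and interview themes by completer status, and present them beside drop-out and compliance.
3. **Reconcile the first UEQ.** Make the text and Table 2 agree, with the first administration following actual use of the system.

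The cost is one call per early leaver, which is 3 to 30 calls if 5% to 50% of 60 stop, plus the wording changes. Some leavers will decline, so selection is reduced but not removed. The headline usability score may also be less favourable.
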